## Exploratory objectives

1. To investigate the effect of celgosivir on the immunological profile of dengue fever patients

Hypothesis: The maximal change from baseline between Day 2 and 5 will be lower for patients taking celgosivir than for those taking placebo for the following cytokines: (a) TNF- (b) IL-6, (c) IL-12, (d) interferon-, (e) IP-10 and (f) MCP-1.

1. To investigate the effect of celgosivir on the use of analgesic medications of dengue fever patients

Hypothesis: Patients taking celgosivir will use less analgesic medications from Day 1 to Day 5 than those taking placebo.

1. To investigate the effect of celgosivir on the intensity of joint and muscle pain of dengue fever patients

Hypothesis: Patients taking celgosivir will experience a lower intensity of joint and muscle pain from Day 2 to Day 5 than those taking placebo.

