## Selection and Withdrawal of Patients

### Inclusion Criteria

1. Male or female, age 21-65 years
2. Fever of  38C (directly measured or patient reported) of  48 hr duration.
3. At least two of the following criteria indicating probable dengue infection:
   1. Live or work in or recent travel to dengue endemic area
   2. Nausea and vomiting
   3. Presence of rash
   4. Aches and pains, including headache, or retro-orbital, muscle or joint pain
4. Positive NS1 strip assay or PCR
5. Able and willing to give written or oral informed consent
6. Willing to be an inpatient for from Study Day 1 to 5, and to return to the IMU on Study Days 7, 10, and 15.
7. Willing to keep a diary of pain medication usage and side effects

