Viral clearance is indicated by an “undetectable” lab test results in the Dengue PCR at baseline, Day 2, Day 3, Day 4, Day 5 and Day 7. The time from baseline to viral clearance will be analyzed using a Kaplan-Meier analysis.

Serum NS 1 is measured by lab test results of “Dengue Non-structure protein 1”. The mean serum NS 1 between day 2 and Day 5 inclusive will be computed for each patient, and compared between the two groups using linear regression, adjusting for primary vs secondary infection. NS1 clearance is indicated by an undetectable lab test result in the NS1 assay. The time to NS1 clearance will be analyzed using a Kaplan-Meier analysis and compared using log rank test.

Leukocyte is measured by lab test results of “Urinalysis”, while platelet count is measure by the lab test results of “Hematology”. Both outcomes will be measured at baseline, Day 2, Day 3, Day 4 and Day 5. The maximum changes from baseline in leukocyte and platelet counts between Day 2 and Day 5 will be computed for each patient, and compared between the two groups using a two-sample t-test.

Hemoconcentration is defined as the hemaocrit at each day compared to that at Day 15. If the reference value at Day 15 is not available, use the value at Day 10. If both values at Day 10 and Day 15 are not available, the patient will be treated as a missing case. The mean maximal hemoconcentration from Day 2 to Day 5 will be computed for each patient, and compared between the two groups using a two-sample t-test.

Clearance celgosivir and volume of distribution of celgosivir will be obtained from concentration-time date by standard PK analysis. The correlation of these PK parameters with weight, age, and sex will be examined by nonlinear mixed effects modeling.

Exploratory outcomes

The various cytokines including TNF-, IL-6, IL-12, interferon-, and MCP-1, are measured by lab test results of “Cytokines” at Study Days 1, 2, 3, 4, 5, 7, 10, and 15. The maximal change from baseline (Day 1) in these cytokines between Day 2 and 15 will be computed for each patient, and compared between the two groups using two-sample t-test.

To investigate whether patients taking celgosivir will use less analgesic medications during the study, analgesic medications recorded during the in-hospital stay and the out-patient diary will between totaled. The total will be compared between the two groups using Fisher exact test.

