To investigate whether patients taking celgosivir will experience a lower intensity of joint and muscle pain during the study, the intensity of joint and muscle pain recorded in the “Pain Score” section during the in-hospital stay and the outpatient diary will be obtained and compared between the two groups using two-sample t-test.

Safety outcome

Safety data will be tabulated according to the standard IMU grading scales for occurrence. The proportion of AEs and SAEs among patients will be reported by cohort.

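### Exploratory analyses do not fit their variables or the stated hypotheses: Fisher's exact test on analgesic totals, conflicting time windows, IP-10 unlisted, and an unclear source for outpatient pain scores

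*Protocol*

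**What the plan says.** **Analgesics.** The hypothesis in Section 2.3 is "Patients taking celgosivir will use less analgesic medications from Day 1 to Day 5 than those taking placebo". Section 5.1 has the date, time and amount of each pain medication recorded. Section 6.2 adds in-hospital use to outpatient diary use and states "The total will be compared between the two groups using Fisher exact test". It gives no cut-off or category.

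**Cytokines.** Section 2.3 says "The maximal change from baseline between Day 2 and 5 will be lower for patients taking celgosivir" for six markers, ending "e) IP-10 and (f) MCP-1". Section 6.2 says "The maximal change from baseline (Day 1) in these cytokines between Day 2 and 15 will be computed for each patient". Its list names TNF, IL-6, IL-12 and interferon, then closes "and MCP-1, are measured by lab test results of" the cytokine panel. IP-10 is not among them.

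**Pain.** The hypothesis in Section 2.3 covers Day 2 to Day 5. Section 6.2 uses pain intensity from the Pain Score section "during the in-hospital stay and the outpatient diary will be obtained" and compares the arms by a two-sample t-test. The inclusion criteria describe the diary as "Willing to keep a diary of pain medication usage and side effects"; Section 3.1 describes it as a record of analgesic use. Pain intensity itself is scheduled on the visual analog scale (VASP), daily in hospital and at the Day 7, 10 and 15 visits (Sections 3.1 and 5.1, Table 2).

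**The concern.** Fisher's exact test compares counts in categories. A summed amount has no categories until someone sets them, so the analyst must either apply the test to a table with one column per distinct total or choose a cut that the protocol does not give. The first is a weak test for a shift in amount; the second discards information and leaves the cut open.

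Separately, the hypotheses and the analyses describe different endpoints. A statistical analysis plan, which the protocol promises before unblinding, cannot follow both. If nobody reconciles the two sections first, two defensible answers exist for each of the three endpoints. Section 3.1 says that the trial will assess whether the VASP and analgesic use are valid measures of drug activity, so how these endpoints are analysed bears on a stated purpose of the trial.

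**Working it through.** The protocol attaches no figure to these endpoints, so there is none to reproduce. Its sample size concerns viremia and is not affected.

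**1. Fisher's test on raw totals**

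- Inputs: 25 patients per arm (Section 3.1); totals as a quantity (Sections 5.1 and 6.2).
- If all 50 totals differ, the table is 2 × 50 with every column total equal to 1 and row totals of 25 and 25. Each possible table has probability 1/C(50, 25). The exact p-value sums the probabilities of all tables no more likely than the observed one, which is all of them, so p = 1 whatever the effect.
- If totals are counted in doses, many will tie and p = 1 no longer follows. Illustration, with assumptions that are not in the protocol: negative-binomial dose counts, dispersion 4, 25 per arm, two-sided 5%. Two separate simulations gave these powers:

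| Mean doses | Exact test on raw totals | t-test |
|---|---|---|
| 6 v 3.5 | 18–22% | 73–78% |
| 4 v 2 | 35–39% | 84–87% |

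**2. Fisher's test on a dichotomised total**

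Assumed: normal totals, two-sided 5%, 25 per arm.

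- Shift of 0.8 SD, t-test: noncentrality = 0.8/√(2/25) = 2.83 on 48 degrees of freedom, which gives power of about 79–80%.
- Same shift, Wilcoxon, by simulation: 77–78%.
- Same shift, Fisher on a median split: significance needs at least 17 of 25 against 8 of 25 above the median (p = 0.023), because 16 against 9 gives p = 0.089. Simulated power is 48–49%.
- Shift of 0.7 SD: t-test 68%. Fisher, with the cut exceeded by 50, 70, 80, 90 or 95% of placebo patients: 38, 42, 34, 25 or 12%.

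**3. Windows and content side by side**

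| Endpoint | Section 2.3 | Section 6.2 |
|---|---|---|
| Analgesics | Day 1–5 | In-hospital stay plus outpatient diary |
| Cytokines: window | Day 2–5 | Day 2–15 |
| Cytokines: named markers | Six, with IP-10 | Five, without IP-10 (open list) |
| Pain | Day 2–5 | In-hospital stay plus outpatient diary |

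The last dose is on Day 5 (hour 96 in Table 2). Under Section 6.2 the cytokine maximum may therefore come from Day 7, 10 or 15, after dosing has ended. The diary likewise covers time after discharge, which is planned for Day 5. The in-hospital stay is not equal to Day 1–5 either, because Section 3.1 provides for patients who remain longer.

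**4. Source of outpatient pain scores**

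Sections 3.1 and 3.2.1 describe the diary as holding analgesic use, or pain medication and side effects. Neither mentions pain intensity. Section 6.2 treats the diary as a source of intensity, although the protocol schedules the VASP at each outpatient visit.

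**The case against.** The strongest reply is that these are exploratory endpoints, that detail is deferred to a statistical analysis plan, and that the wider windows may be deliberate: Section 6.2 frames the analgesic and pain questions as covering the study as a whole, and Table 2 collects cytokines and VASP to Day 15. That limits the consequence and means the protocol does not prove which window was meant. It does not remove the conflict, because the protocol itself states both versions.

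Four stronger readings are tempting, and the protocol does not support them:

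- *The analgesic test can never show an effect.* This is true only if all totals differ. With tied totals the power is poor but not zero, and Fisher's test would be sound for a defined category such as any use against none.
- *IP-10 has been removed.* The list in Section 6.2 is introduced as an inclusive one, and nothing deletes the marker. It is unlisted, possibly by oversight.
- *The diary holds no pain scores.* The diary form is not shown, and the two descriptions are one line each. They show only that the descriptions and the analysis text disagree.
- *Later days dilute any effect.* No calculation shows this. A maximal change is unaffected by later days when the peak falls within Day 2–5, and no section says that illness has ended by Day 7.

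The choice between a t-test and a Wilcoxon test is largely preference, as their similar power shows.

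**Conclusion.** The point holds as a mismatch between test and variable for analgesics, and as an inconsistency between Sections 2.3 and 6.2 for three endpoints. For analgesics, a dichotomised total costs roughly 30 percentage points of power in the 0.8 SD median-split illustration (about 80% down to about 48%). That figure depends on the assumed normal totals, shift and cut. For cytokines and pain no loss can be quantified from the protocol; the finding is that the analysis and the hypothesis define different endpoints. The missing IP-10 entry and the diary as pain source are matters of clarification. The primary analysis and the sample size are untouched, and the severity is minor.

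**What to change.** Amend Section 6.2, or settle the points in the statistical analysis plan before unblinding:

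- Compare the total analgesic amount by a Wilcoxon rank-sum test or a t-test. Keep Fisher's exact test only for a defined category such as any use against none.
- Give each endpoint one window. The windows in Section 2.3 (Day 1–5 for analgesics, Day 2–5 for cytokines and pain) are the natural choice: they are the stated hypotheses, and Section 6.2 itself uses Day 2–5 for NS1, leukocytes, platelets and hemoconcentration. Show later days descriptively.
- Add IP-10 to the cytokine list.
- Name the VASP as the source of pain intensity, in hospital and at outpatient visits.

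The cost is wording only. The analgesic amounts, cytokine samples and VASP scores needed are already scheduled.

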Fifty (50) patients will be randomized 1:1 to celgosivir or placebo. Capsules of placebo or celgosivir will be administered for 5 days. Patients will be given an initial loading dose of 400 mg followed by a maintenance dose of 200 mg every 12 hr for a total of nine (9) doses. Drug should be taken 1 hr before consuming food or 2 hr afterwards. Patients will be placed on a special diet of protein, vitamins, and glucose containing minimal complex sugars or starches. Oral intake of fluids will be recorded. While in hospital from Day 1 to Day 5, daily clinical exams will be conducted, and blood samples will be collected for plasma viral load, NS1, hematology, clinical chemistry, cytokine levels and safety observations. During this period, eight serum samples will be obtained for drug levels. On Study Day 5, after blood draws, administration of the last dose, safety assessments, determination of risk for DHF or DSS, and satisfactory clinical status, the patient will be discharged. Patients at risk for or who have dengue hemorrhagic fever (DHF) or dengue shock syndrome (DSS) will remain in hospital until fit for discharge. Patients who progress to DHF or DSS may require intravenous fluids, platelet and/or blood transfusions and evaluations from other clinical specialists. At discharge, the patient will be asked to return on Study Days 7, 10, and 15 for blood sampling and safety assessments. Patients will complete visual analog scales for joint and muscle pain (VASP), and be evaluated for safety and tolerability daily while in hospital and at each subsequent outpatient visit. While in hospital, concomitant usage of analgesics will be recorded. As an outpatient, patients will keep a diary of concomitant usage of analgesics. If the patient remains in hospital past day 5, planned outpatient study assessments will be collected in hospital.

The patient will complete the study on Study Day 15 after the investigator has completed the final assessment, unless ongoing adverse events require monitoring. For subjects prematurely terminating participation in the study, assessments planned for Study Day 15 will be obtained if possible, and study completion evaluations must be performed.

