## Statistical analysis

A detailed statistical analysis plan will be prepared prior to unblinding.

General

Continuous variables will be summarized using mean and standard deviation. Categorical variables will be summarized by frequency and percentage. Percentages will be rounded to one decimal place and, therefore, may not always add up to 100. All statistical tests will be set at a 5% level of significance. All confidence intervals will be 95% and two-sided. Statistical analyses will be performed using SAS version 9.3.

Demographic and baseline characteristics

Descriptive statistics will be used to summarize demographics and baseline information and to assess balance between the two groups (mean, standard deviation, minimum, maximum, and median for continuous variables; frequency and percent for categorical variables).

Analysis population

Statistical analysis for efficacy data will be carried out on an intention-to-treat (ITT) basis. An ITT set is defined as all patients who signed the informed consent form for the study enrollment and obtained an enrollment number. The treatment group of patients in the ITT set is the planned treatment group, i.e., according to the randomization list planned prior to the study commencement.

Statistical analysis for safety data will be carried out on an as-treated basis. An as-treated set is defined as all subjects who signed the informed consent form for the study enrollment and obtained an enrollment number. The treatment group of patients in the as-treated set is according to the treatment actually received.

Primary outcome

The primary outcomes include the mean of virological log reduction at Day 2, Day 3 and Day 4 and fever AUC above baseline. The virological log reduction of each patient will be measured at Day 2, Day 3 and Day 4 when they are inpatients. The mean of these three measurements will be computed for each patient, and then be compared between the two groups by a two-sample, one-sided t-test. The body temperature of each patient will be measured at baseline and from Day 1 to Day 5, and a curve of the temperature will be plotted. The area under this curve but above the baseline value will be computed for each patient, and then be compared between the two groups by a two-sample, one-sided t-test.

Secondary outcomes

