| Viremia | + | |  |  |  | + |  |  |  | + |  |  |  | + |  |  |  | + |  |  | + |  |  |
| Quantitative NS1 | + | |  |  |  | + |  |  |  | + |  |  |  | + |  |  |  | + |  |  | + | + | + |
| Immunological Profile (Cytokines) | + | |  |  |  | + |  |  |  | + |  |  |  | + |  |  |  | + |  |  | + | + | + |
| ~~DNA~~ | ~~+~~ | |  |  |  |  |  |  |  |  |  |  |  |  |  |  |  |  |  |  |  |  |  |
| RNA | + | |  |  |  | + |  |  |  | + |  |  |  | + |  |  |  | + |  |  | + | + | + |
| PK samples - serum e | + | |  |  |  | + |  | + |  | + |  | + |  | + |  | + |  | + |  |  |  |  |  |
| PK sample - urine f | + | |  |  | + | + | + |  | + | + |  |  | + | + |  |  | + | + |  |  |  |  |  |
| Visual Analog Scale for Pain | + | |  |  |  |  |  | + |  |  |  | + |  |  |  | + |  |  |  | + | + | + | + |
| Record Fluid Administration |  | |  | + |  |  |  | + |  |  |  | + |  | + |  | + |  |  |  | + |  |  |  |
| Verify Urine production (I/O)c |  | |  | + |  |  |  | + |  |  |  | + |  | + |  | + |  |  |  | + |  |  |  |
| Record Adverse Events |  | |  | + |  |  |  | + |  |  |  | + |  |  |  | + |  |  |  | + | + | + | + |
| Record Stool Freq & Consistency & Flatulence |  | |  | + |  |  |  | + |  |  |  | + |  |  |  | + |  |  |  | + | + | + | + |
| Record Pain Medications | + | |  | + |  |  |  | + |  |  |  | + |  |  |  | + |  |  |  | + | + | + | + |
| Record Other Concomitant Meds | + | |  | + |  |  |  | + |  |  |  | + |  |  |  | + |  |  |  | + | + | + | + |

Annotations:

a Height to be performed at screening visit only

b 2 hourly temperature monitoring

c6 hourly BP, PR, O2 saturation and I/O monitoring

d Group and Cross March (GXM) to be perform if clinical indication by study investigator only

e PK samples – serum perform at (Pre-dose, 23hr(+/-1hr) , 25 hr(+/-0.5hr), 47hr(+/-1hr), 49.5hr(+/-0.5hr), 71hr(+/-1hr), 74hr(+/-1hr)and 95hr(+/-1hr))

f PK sample – urine perform at (Pre-dose, 0 – 12hr, 12hr – 24hr, 24h – 36hr, 36hr – 48hr, 48hr – 60hr, 60hr – 72hr, 72hr – 84hr, 84hr – 96hr)

g Any subject who has a platelet count drop of ≥50,000/mm3 over a 24 hour period will require FBC monitoring every 12 hr henceforth until platelet count trend reverses.

h Clinical exam will be performed twice a day (except for Study Day 5).

| Send collected samples to Duke-NUS |
| --- |
| Send PK samples to [name] @ NUS |

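### The exploratory pain analysis names a two-sample t-test but no per-patient summary, covers a different window from its own hypothesis, and leaves the pre-dose score unused

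*Protocol*

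**What the plan says.** Section 3.1 (Summary) sets up repeated scoring: "Patients will complete visual analog scales for joint and muscle pain (VASP), and be evaluated for safety and tolerability daily while in hospital", and again at each outpatient visit. In Table 2 the row "Visual Analog Scale for Pain" has eight marks: one before the first dose, one on each of Days 2, 3, 4 and 5, and one on each of Days 7, 10 and 15. Section 5.1 also places the first score before randomization.

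The hypothesis in section 2.3 has a fixed window: "Patients taking celgosivir will experience a lower intensity of joint and muscle pain from Day 2 to Day 5 than those taking placebo".

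The analysis in section 6.2 (Exploratory outcomes) asks instead whether treated patients "will experience a lower intensity of joint and muscle pain during the study". It says that the intensities recorded in hospital and in the outpatient diary "will be obtained and compared between the two groups using two-sample t-test". It gives no per-patient summary, time point, covariate or sidedness.

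Elsewhere section 6.2 is more explicit. For the virological primary outcome it says: "The mean of these three measurements will be computed for each patient, and then be compared between the two groups". Fever AUC, NS1, leukocytes, platelets, hemoconcentration and cytokines are likewise computed for each patient before comparison.

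**The concern.** A two-sample t-test needs one independent value per randomized unit. Patients are the randomized unit, and each supplies up to eight correlated scores. Pain is the only repeated continuous outcome in section 6.2 compared by t-test or regression for which the step from scores to patient is missing. The protocol thus names a test whose input is undefined, and its two statements of the window give different inputs: four scores under section 2.3, and seven or eight under section 6.2, depending on whether the pre-dose score counts as an in-hospital score.

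Two things are at stake. An analyst who took the sentence at face value could run a test that overstates the evidence. Even with a sound per-patient summary, an unadjusted comparison gives up precision that a score already collected would supply. Section 3.1 says the trial will examine whether the pain scale is valid as a further measure of drug activity, so the result may inform later endpoint choice. No primary or secondary conclusion depends on it.

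**Working it through.** **The plan's own figures.** For pain the only stated figure is the nominal 5% level. The one design calculation (section 6.1) concerns viremia. It reproduces: at a difference of 1 SD and one-sided 5%, the noncentral t gives 79.7% power with 13 per group and 82.4% with 14, so 14 is right. It does not bear on this point.

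**Inputs from the protocol.** There are 25 patients per arm. The number of scores per patient is m = 4 (Days 2 to 5), 7 (all post-dose) or 8 (all). The level is 5%, with sidedness not stated for this test.

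**Assumed input.** The protocol gives no within-patient correlation (ICC). I use 0.2 to 0.5 as the main range and wider values as a check.

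**1. If all scores were pooled as independent.** The variance is understated by the design effect D = 1 + (m − 1) × ICC. The actual error rate is then 2 × [1 − Φ(1.96/√D)] two-sided, or 1 − Φ(1.645/√D) one-sided.

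For m = 4:
- ICC 0.2: D = 1 + 3 × 0.2 = 1.6 and √D = 1.265. Two-sided 1.96/1.265 = 1.549, giving 12.1%. One-sided 1.645/1.265 = 1.300, giving 9.7%.
- ICC 0.5: D = 2.5 and √D = 1.581. Two-sided 1.240, giving 21.5%. One-sided 1.040, giving 14.9%.

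The same formula for the other counts, with ICC 0.2 to 0.5:

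| Scores pooled | Two-sided | One-sided |
|---|---|---|
| 4 | 12–22% | 10–15% |
| 7 | 19–33% | 13–21% |
| 8 | 21–36% | 14–22% |

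Simulation (20,000 null trials per setting) agrees; for example, 22.0% for m = 4 and 35.7% for m = 8 at ICC 0.5, two-sided. Two variants with m = 8, two-sided:
- Correlation decaying with days between visits: 16% at a daily correlation of 0.5, 25% at 0.7, 32% at 0.8 and 40% at 0.9.
- A strong common fall in pain over time, which widens the pooled SD: 7 to 19% at ICC 0.2 to 0.5.

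The largest two-sided value computed is 44.6% (m = 8, ICC 0.8).

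**2. If one mean per patient is tested.** Simulated error stays at about 5% (4.8 to 5.3% two-sided) at every correlation tried.

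**3. Value of the pre-dose score.** Take scores of unit variance and equal correlation ρ, with four post-dose scores. The patient mean has variance (1 + 3ρ)/4. Adjusting for baseline removes ρ². The fraction removed is 4ρ²/(1 + 3ρ).
- ρ = 0.5: variance 2.5/4 = 0.625, less 0.25 leaves 0.375; 0.25/0.625 = 40%.
- ρ = 0.3: 0.36/1.9 = 19%.
- ρ = 0.7: 1.96/3.1 = 63%.

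For an illustrative difference of 0.6 SD at ρ = 0.5 (noncentral t, 48 df, two-sided 5%), power is 75% unadjusted and 92% adjusted.

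**4. Effect of the window.** Suppose, for illustration, that treatment lowers pain by δ on Days 2 to 5 only. The Day 2 to 5 mean carries δ, the mean of seven post-dose scores 4/7 × δ = 0.57δ, and the mean of all eight 4/8 × δ = 0.50δ. The choice between the two windows therefore changes what is estimated.

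**The case against.** The strongest reply is that the protocol never says scores are pooled. Every neighbouring repeated outcome is reduced to one value per patient, so the pain sentence may simply be shorthand for the same approach. Section 6.2 also defers detail to an analysis plan to be written before unblinding, and the summary measure for an exploratory endpoint is a natural thing to leave there. This stands: pooling is one reading of silent text, and a per-patient mean fits the words equally well.

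A reader might go further and infer that the plan fixes an invalid test with a false-positive rate of 20 to 35%. The document does not support that. The range needs pooling, about seven or eight scores per patient, a two-sided test, an assumed correlation of roughly 0.2 to 0.5 and no strong time trend. None of these is stated, and the hypothesis's own window has four scores.

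A reader might also blame the unused baseline for a raised false-positive rate. That is wrong: in a randomized comparison an unadjusted t-test on one value per patient is valid, only less precise.

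The reply does not remove two points. The windows in sections 2.3 and 6.2 differ on the page. The method that the protocol does name is unadjusted although a pre-dose score is collected.

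**Conclusion.** The point holds as a low-severity matter on an exploratory endpoint. The conflict between the two windows, the missing per-patient summary and the unused pre-dose score can all be read directly from the protocol and need no assumption.

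The inflated error is conditional. It arises only if scores are pooled, and its size depends on the number of scores, the sidedness and a correlation that the protocol does not give. The precision loss is also conditional on an assumed correlation, but it applies to any unadjusted per-patient comparison: 40% of the variance at 0.5, with 19 to 63% over 0.3 to 0.7.

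**What to change.** Reconcile the window in section 6.2 with the Day 2 to Day 5 hypothesis in section 2.3, and replace the pain sentence with:

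*For each patient, the mean VASP score over Study Days 2 to 5 will be computed and compared between groups by ANCOVA, adjusting for the pre-dose VASP score.*

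State whether the test is one- or two-sided. If Days 7, 10 and 15 are also to be analysed, use a mixed model for repeated measures with treatment, visit, treatment-by-visit and baseline terms and a within-patient covariance.

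The cost is one sentence in the protocol or the analysis plan, settled before unblinding. No new data are needed, since the pre-dose and daily scores are already scheduled. The interval will be wider than a pooled test would show, but it will be correct.
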